### Allocation, randomisation, and blinding

Participants will be allocated into two groups (intervention and control) and stratified randomisation will be performed to ensure homogeneity between the groups (1:1). Stratification will consider participants’ self-assigned codes along with sociodemographic and professional characteristics such as sex, age, educational background, professional category, total professional experience, experience in primary health care, and the type of unit where they work. Stratified randomisation will be executed using RANDOM.ORG by an independent researcher uninvolved in the PPAPEP intervention or data analysis, because it offers true random numbers that are for many purposes better than the pseudo-random number algorithms typically used in traditional computer statistical software. Regarding the randomisation during each evaluation point, questionnaires will be completed by participants, sealed in opaque envelopes labelled with the respective evaluation moment ('EM0', 'EM1', 'EM2, or 'EM3'). After the final evaluation moment ('EM3'), the questionnaires will be selected based on the administration timeline illustrated in Figure 1. This approach enables participants to choose their preferred day and time for sessions without compromising group homogeneity or randomisation. It also minimises selection and information bias by ensuring that neither the researcher nor the participants are aware of their allocation until data collection is complete. Assessments during the intervention were conducted using self-administered questionnaires, and participants were instructed not to share session information with others.

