### Sample size

Considering the study’s objective, we calculated the sample size using G*Power software (version 3.1.9.6) with a two-tailed test to compare two dependent means (Student’s *t*-test). The parameters used included an effect size of 0.5, a significance level (α) of 0.05, and a statistical power (1-β) of 0.80. The calculation suggests a minimum total sample size of 34 participants (17 participants per group). The allocation ratio between the groups will be 1:1. Thus, we aim to recruit at least 34 nurses working in primary healthcare units who are interested in and agree to participate in the study.

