### Data security and management

Questionnaires will remain anonymous, and data analysed in aggregate form and access restricted to the research team. Each participant will create a unique and confidential code to link pre- and post-intervention responses, ensuring anonymity. The research team will securely store the database with password protection, accessible only to investigators.

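### Stratifying at least 34 nurses on seven characteristics gives 128 or more cells, so the scheme acts nearly like simple randomisation and cannot ensure the balance the protocol promises

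*Protocol article*

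**What the plan says.** Under Allocation, randomisation, and blinding, the protocol article states that "stratified randomisation will be performed to ensure homogeneity between the groups (1:1"). Stratification is to take account of the codes that nurses give themselves, "along with sociodemographic and professional characteristics such as sex, age, educational background, professional category, total professional experience, experience in primary health care"; type of unit is the seventh characteristic named. An independent researcher is to carry it out with RANDOM.ORG. No minimisation, matching or other covariate-adaptive method is named.

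Under Sample size: "The calculation suggests a minimum total sample size of 34 participants (17 participants per group"), and "The allocation ratio between the groups will be 1:1". Under Data security and management: "Each participant will create a unique and confidential code", whose stated purpose is to link a participant's questionnaires over time.

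Under Data analysis, Student's t-test is named for comparing group means on the primary outcomes. Linear regression is planned as a further multivariable analysis.

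**The concern.** Stratification balances the arms only where a stratum holds at least two people. With seven factors and about 34 nurses, most occupied strata would hold one person, whose assignment is then a toss of the coin. The scheme would add complexity and return little of the balance it is meant to give.

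Two things are at stake. First, baseline differences between the arms could arise by chance and pass straight into the unadjusted t-tests. Second, the article treats homogeneity as secured: the same section relies on it when it argues that letting nurses choose their session day does no harm to the comparison. A reader would take from this a guarantee of comparability that the method does not provide.

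**Working it through.** **Inputs from the protocol article.** Minimum N = 34, 17 per group, ratio 1:1 (Sample size); seven named characteristics and a unique personal code (Allocation, randomisation, and blinding; Data security and management). **Assumed, because the article does not give them:** the number of levels per factor, how the nurses are distributed over them, and the block size.

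**1. The plan's own figure.** The stated inputs are a "two-tailed test to compare two dependent means" with "an effect size of 0.5, a significance level (α) of 0.05, and a statistical power (1-β) of 0.80". Exact noncentral-t power for a paired test is 0.795 at 33 pairs and 0.808 at 34, so 34 reproduces. (It is a number of pairs; whether it supports 17 per group is a separate matter and is not used here.)

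**2. Number of cells.** With the fewest possible levels, 2^7 = 128, and 34/128 = 0.27 nurses per cell. With three levels for every factor except sex, 2 × 3^6 = 1,458. No choice of cut-points gives fewer than 128. Even four nurses per cell would need 4 × 128 = 512.

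**3. Occupancy with equally likely cells.** Expected occupied cells: 128 × (1 − (127/128)^34) = 30.0. Probability that a nurse is alone: (127/128)^33 = 0.772, so 34 × 0.772 = 26.2 of 34 nurses.

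**4. Arm sizes.** These are simulated (100,000 runs per stratified row) with blocks of 2 within cells and no overall constraint on the list. Simple randomisation is exact: C(34,17)/2^34 = 0.136 and 2 × P(Bin(34, 0.5) ≤ 14) = 0.392.

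| Scheme and assumed factor distribution | Nurses alone | Exactly 17:17 | Difference of 6 or more |
|---|---|---|---|
| Seven binary factors, equal and independent | 77% | 15% | 33% |
| Seven, uneven (0.85, 0.5, 0.7, 0.6, 0.5, 0.5, 0.6) | 64% | 17% | 29% |
| Seven, four strongly correlated, as age and experience would be | 46% | 19% | 23% |
| Seven, strongly skewed (0.9, and 0.8 six times) | 34% | 21% | 17% |
| Simple randomisation | – | 14% | 39% |
| One binary stratifier | 0% | 75% | 0% |

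If the unique code were itself a stratifier, every stratum would hold one person and the scheme would be exactly simple randomisation.

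**5. Baseline balance.** This assumes seven independent 50:50 factors and blocks of 2 in all 128 cells. A given factor differs between arms by 20 percentage points or more in 19% of simulated trials, against 25% under simple randomisation. At least one of the seven does so in 77%, against about 86%.

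**6. Power cost of unequal arms.** For a two-sided two-sample t-test at d = 0.5, power is 0.293 with 17:17 and 0.285 with 14:20. At d = 1.0 it is 0.807 and 0.795. The loss is about one percentage point.

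**The case against.** Several stronger readings are tempting, and the documents do not support them.

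- **That a 1:1 ratio is impossible.** Simple randomisation still allocates 1:1 in probability, and an equal split can occur by chance. Table 2 places allocation at EM0, after consent, so a full list may have been available and 17:17 could have been forced, for instance by pooling the single-person strata. The article does not say. The arm-size figures are therefore conditional on there being no overall constraint.
- **That the code makes every stratum a single person.** Its stated purpose is to link questionnaires. The natural reading is that the independent researcher worked from coded records. The wording should be cleared up, but the argument does not need the code.
- **That the collapse to simple randomisation is complete.** Skewed or correlated factors leave some real balancing, as the table shows.
- **That unequal arms cost appreciable power.** They do not.

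It can also be said that block sizes and cut-points belong in a fuller protocol, that the factor list is only illustrative, and that taking factors into account could loosely describe minimisation. The first is right, and their absence is no criticism. But 128 is a floor that no cut-points can lower, and the method the article names is stratified randomisation, with nothing covariate-adaptive mentioned. The 34 is a minimum, yet nothing in the article suggests numbers near 512. Finally, chance imbalance here is no worse than under ordinary simple randomisation, and a regression is planned. That limits the harm; it does not make the assurance true.

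**Conclusion.** The concern holds in a limited form. Stratifying about 34 nurses on seven characteristics cannot ensure homogeneous groups, nor an equal split unless the list is constrained overall. Under plausible distributions, about half to three quarters of the nurses gain nothing from the stratification; under strongly skewed factors it is still about a third. The cell count rests on the article alone. The balance percentages rest on assumed factor distributions and on blocks of 2; across every distribution tried, an exact split stays at or below about 21%.

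The consequence is chance baseline imbalance in a small trial whose primary group comparison is an unadjusted t-test, and an overstated claim of comparability. It does not invalidate the randomisation. It should be corrected, and doing so is cheap.

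**What to change.** 1. State that the self-assigned code is only an identifier and is not used to form strata.
2. If allocation is still open, have the same independent researcher use permuted blocks stratified by one factor already collected before allocation (type of unit, for example), or minimisation with a random element on two or three such factors. The EM0 score is not suitable for this, because completed questionnaires are sealed until after EM3.
3. If allocation is done, which is likely since recruitment took place in September and October 2024, describe how it was carried out, call it effectively unstratified, and remove the assurance that the groups will be homogeneous.
4. In either case, make the between-group comparison a linear regression on arm, adjusted for the EM0 score and the stratification factor or factors used (or type of unit, if allocation was effectively unstratified).

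The cost is a change to the randomisation list or to its description, and a few degrees of freedom in the model; no extra staff or data are needed. The downside is that factors left out are balanced only by chance, as they nearly are now.

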### Intervention group

The intervention group will participate in the PPAPEP, which will be delivered in-person by a trained member of the research team in a designated room within the study site. The evaluations for this group will occur at pre-intervention ('EM0'), post-intervention ('EM2'), and 3 months' post-programme ('EM3'), as shown in Figure 1.

### Control intervention

For the control group, evaluations will be conducted at pre-intervention ('EM0') and before the intervention sessions ('EM1'). Although they will eventually participate in the programme, only evaluations preceding the intervention will be considered.

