**Method:**

The intervention group will participate in the PPAPEP, consisting of six training sessions, each lasting 3 hours. The programme’s goal is to empower nurses by providing knowledge about what constitutes a positive nursing practice environment and equipping them with tools to improve their practice environment. The outcomes of the intervention will be assessed both at the end of the programme and 3 months after its conclusion.

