### Outcomes evaluation

Participants will complete a sociodemographic questionnaire, and the programme’s effectiveness will be assessed using two instruments: the shortened version of the Scale for the Environments Evaluation of Professional Nursing Practice (SEE-Nursing Practice)^
39
^ and Safety Attitudes Questionnaire (SAQ) — Short Form.^
40
^

The SEE-Nursing Practice consists of 59 items across three subscales: structure (29 items); process (19 items); and outcome (11 items). Participants rate each item on a five-point Likert scale (1: never to 5: always). Higher scores indicate a more favourable NPE for care quality and professional wellbeing. Scores are interpreted as follows:<35% (unfavourable), 35–55% (moderately favourable), 55–75% (favourable), and>75% (very favourable).^
39
^

The SAQ — Short Form 2006 assesses healthcare professionals' perceptions of patient safety attitudes. It has been previously validated and culturally adapted to the context in which the study will be conducted.^
40
^ The SAQ — Short Form 2006 comprises six dimensions, addressing organisational factors, work environment factors, and team factors, with a total of 30 items. Participants respond to each item using a five-point Likert scale ('strongly disagree' to 'strongly agree'). The final score ranges from 0–100, where 0 represents the worst perception and 100 the best perception of the safety climate.^
40
^ The timing of the outcome measures and data collection evaluation moments are detailed in Table 2, following SPIRIT guidelines and the extension for reporting trial protocol outcomes.^
36
^

**Table 2. table2:** Outcome measures and data collection evaluation moments

Activity	Study period					
	T – 1 (Pre-allocation)	EM0 (baseline)	EM1 (pre-intervention)	Intervention period	EM2 (post-intervention)	EM3 (follow-up)
Enrollment						
- Participants' information	X					
- Participants express interest in PPAPEP	X					
- Participant consent	X					
- Random group allocation		X				
Intervention: PPAPEP			—	—	—	—
Outcomes						
Data collection:						
- Demographic and professional data	X					
- Scale for the Environment's Evaluation of Professional Nursing Practice — Shortened Version		X	X		X	X
- Safety Attitudes Questionnaire — Short Form		X	X		X	X
- Qualitative data from participants’ knowledge during intervention				X		

EM = evaluation moment. PPAPEP = Positive Nursing Practice Environments Promotion Programme

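### The 3-month outcome has no control observation, and the post-programme contrast is concurrent only if Figure 1 (not shown) aligns control EM1 with intervention EM2

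*Protocol article*

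**What the plan says.** The two arms have different assessment schedules.

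- **Control intervention:** "For the control group, evaluations will be conducted at pre-intervention ('EM0') and before the intervention sessions ('EM1". The section continues: "Although they will eventually participate in the programme, only evaluations preceding the intervention will be considered".
- **Intervention group:** "The evaluations for this group will occur at pre-intervention ('EM0'), post-intervention ('EM2'), and 3 months' post-programme ('EM3". EM1 is not listed for this arm.
- **Abstract, Method:** "The outcomes of the intervention will be assessed both at the end of the programme and 3 months after its conclusion".
- **Outcomes evaluation, Table 2:** one timeline without separate rows for the arms. The column "EM1 (pre-intervention" stands before the intervention period; EM2 and EM3 stand after it.
- **Allocation, randomisation, and blinding:** envelopes are labelled by evaluation moment, and "After the final evaluation moment ('EM3'), the questionnaires will be selected based on the administration timeline" in Figure 1. The same section says that neither researcher nor participants learn the allocation before data collection has ended.
- **Data analysis:** a Student's t-test compares the groups, and a paired t-test examines change within groups. The section does not say which moments enter which test.

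**The concern.** A randomised comparison needs both arms observed at the same point, one with the programme and one without. Here the effect is to be judged at two moments, EM2 and EM3, and the control arm is analysed at neither.

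For the 3-month outcome, a change from EM0 to EM3 in the intervention arm will contain everything that moved nurses' perceptions over that period: staffing, season, familiarity with the questionnaires, expectation. Nothing in the plan can separate these from the programme.

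For the end-of-programme outcome, the group t-test can only set intervention EM2 against control EM1. If EM1 falls earlier in the calendar than EM2, any drift between the two is counted as programme effect. If every nurse also fills in every envelope, the intervention nurses will have completed one more round of the instruments by then. At stake is whether the trial can claim a randomised effect at either of its stated outcome times.

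**Working it through.** **Step 1: which moments are used in which arm.**

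| Moment | Intervention | Control |
|---|---|---|
| EM0 (baseline) | used | used |
| EM1 | not listed | used |
| EM2 (end of programme) | used | not used |
| EM3 (3 months after) | used | not used |

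The only shared row is EM0.

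**Step 2: EM3.** The control arm has one assessment after baseline. The intervention arm has two, separated by 3 months. One control assessment cannot match both. Its number and its place in Table 2 put it ahead of EM2, so EM3 is the moment left without a control. Later control questionnaires cannot fill the gap: the protocol excludes them, and those nurses also attend the programme.

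**Step 3: EM2.** The available contrast is intervention EM2 minus control EM1. Randomisation balances the arms at EM0. If scores drift by x SD between the calendar time of EM1 and that of EM2, the expected contrast is programme effect + x. Adjusting for EM0 does not remove x, because x arises after baseline. If EM1 and EM2 fall on the same dates, x = 0.

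**Step 4: size, as an illustration.** The documents give no drift figure, so a range is assumed.

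*Check of the method on the plan's own figure.* Sample size states a two-tailed test of two dependent means, effect size 0.5, alpha 0.05, power 0.80, giving 34. The exact noncentral t for a paired test gives 34 pairs with power 0.808, so 34 reproduces. It reproduces as 34 pairs, not as 17 per group, which is a separate matter.

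*Inputs:* n = 17 per group (Sample size), two-sided alpha 0.05, no programme effect, drift x in SDs of the outcome (assumed).

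*Formula:* rejection rate = P(|T| > critical value), where T is noncentral t with df = 2n − 2 = 32 and noncentrality λ = x·√(n/2) = x·√8.5 = 2.915x.

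| Assumed drift x (SD) | λ | False-positive rate |
|---|---|---|
| 0 | 0 | 5.0% |
| 0.1 | 0.292 | 5.9% |
| 0.2 | 0.583 | 8.7% |
| 0.3 | 0.875 | 13.6% |
| 0.5 | 1.458 | 29.3% |

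This is a bias, so more nurses would not help. With 64 per group and x = 0.2, λ = 0.2·√32 = 1.131 and the rate is 20.2%, against 8.7% with 17 per group.

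**The case against.** **The timing may be sound.** Figure 1 holds the timeline and is not shown. Controls have two assessments before their sessions and join the programme later, which is how a waiting-list arm would look. Table 2 does not separate the arms, and its programme row carries dashes under EM1, the intervention period, EM2 and EM3, so its column order does not settle the calendar. This stands. A reader might infer that the EM2 result is certainly confounded with time; the documents do not establish that. They do lean that way: one common timeline, and an allocation unknown to everyone until data collection ends, which is hard to square with one arm visibly waiting.

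**Not every nurse necessarily fills in all four envelopes.** A reader might infer from the late selection of questionnaires that everyone follows one schedule and that randomisation merely decides whose forms are kept. The protocol never says that each nurse completes every moment, and the arm sections list three and two. That reading is possible but unproven.

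**No between-group test at EM3 is promised.** This is correct. The protocol says only that outcomes will be assessed then, and it plans paired tests within groups. A reader might infer that the 3-month change will be presented as a randomised effect; the text does not say so. But it names 3 months as an outcome time in a randomised trial of effectiveness and nowhere labels that result as uncontrolled.

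**The drift values are assumed.** They are, and at 0.1 SD the inflation is slight. The table shows sensitivity; it does not predict what will happen.

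**Conclusion.** The point holds in two parts of different strength.

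- **EM3: firm.** On the schedules stated for the two arms, no control observation exists at 3 months. The result can describe change within the intervention group and nothing more. A separate analysis plan could not repair this, because the protocol itself rules that "only evaluations preceding the intervention will be considered" for controls.
- **EM2: conditional.** On the text, control EM1 precedes and intervention EM2 follows the programme period, so the contrast carries elapsed time. It becomes a valid concurrent comparison if the two were completed on the same dates before controls began their sessions. If they were not, the false-positive rate with 17 per group runs from 5.9% at an assumed 0.1 SD drift to 29.3% at 0.5 SD, against a nominal 5%.

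The rates assume no programme effect, an unadjusted t-test on scores with equal variances, and drift common to all nurses.

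**What to change.** 1. Label EM3 as an uncontrolled, within-group description of maintenance and remove it from effectiveness claims.
2. Name intervention EM2 against control EM1, adjusted for EM0, as the confirmatory comparison. State the calendar window of each, and confirm that both fall in the same window and before the control group's first session. Reconcile Table 2, and the statement on concealment under Allocation, randomisation, and blinding, with that schedule.
3. If the two were not concurrent, claim no randomised effect and report a before-after study. Use all available EM0 to EM3 data in a mixed model with time. Where the same nurses have EM0, EM1 and EM2, a double-pretest contrast is possible: (EM2 − EM1) − k·(EM1 − EM0), with k the length of the EM1 to EM2 interval divided by that of EM0 to EM1. It removes drift only if drift is linear, and that assumption should be stated.

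**Cost:** changes of wording and analysis, with no new data. Recruitment ran in September and October 2024 and part of the text describes assessments in the past tense, so the dates may only be reportable, not changeable. The 3-month claim becomes weaker, and the end-of-programme claim may too. Naming a between-group contrast also shows that the sample size was computed for a paired test: with 17 per group, an unadjusted t-test has 29% power for a difference of 0.5 SD. That needs its own answer.

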### Outcomes evaluation

Participants will complete a sociodemographic questionnaire, and the programme’s effectiveness will be assessed using two instruments: the shortened version of the Scale for the Environments Evaluation of Professional Nursing Practice (SEE-Nursing Practice)^
39
^ and Safety Attitudes Questionnaire (SAQ) — Short Form.^
40
^

The SEE-Nursing Practice consists of 59 items across three subscales: structure (29 items); process (19 items); and outcome (11 items). Participants rate each item on a five-point Likert scale (1: never to 5: always). Higher scores indicate a more favourable NPE for care quality and professional wellbeing. Scores are interpreted as follows:<35% (unfavourable), 35–55% (moderately favourable), 55–75% (favourable), and>75% (very favourable).^
39
^

The SAQ — Short Form 2006 assesses healthcare professionals' perceptions of patient safety attitudes. It has been previously validated and culturally adapted to the context in which the study will be conducted.^
40
^ The SAQ — Short Form 2006 comprises six dimensions, addressing organisational factors, work environment factors, and team factors, with a total of 30 items. Participants respond to each item using a five-point Likert scale ('strongly disagree' to 'strongly agree'). The final score ranges from 0–100, where 0 represents the worst perception and 100 the best perception of the safety climate.^
40
^ The timing of the outcome measures and data collection evaluation moments are detailed in Table 2, following SPIRIT guidelines and the extension for reporting trial protocol outcomes.^
36
^

**Table 2. table2:** Outcome measures and data collection evaluation moments

Activity	Study period					
	T – 1 (Pre-allocation)	EM0 (baseline)	EM1 (pre-intervention)	Intervention period	EM2 (post-intervention)	EM3 (follow-up)
Enrollment						
- Participants' information	X					
- Participants express interest in PPAPEP	X					
- Participant consent	X					
- Random group allocation		X				
Intervention: PPAPEP			—	—	—	—
Outcomes						
Data collection:						
- Demographic and professional data	X					
- Scale for the Environment's Evaluation of Professional Nursing Practice — Shortened Version		X	X		X	X
- Safety Attitudes Questionnaire — Short Form		X	X		X	X
- Qualitative data from participants’ knowledge during intervention				X		

EM = evaluation moment. PPAPEP = Positive Nursing Practice Environments Promotion Programme

